## Abstract

**Background:**

Success rate of transcatheter aortic valve replacement (TAVR) in aortic regurgitation (AR) patients is relatively low on account of the absence of calcified anchoring structures. Morphological classification and corresponding TAVR strategies for AR are lacking yet.

**Methods:**

The AURORA study is a prospective, multicenter, single-arm cohort study to evaluate the safety and efficacy of transfemoral TAVR for severe AR in patients with high or prohibitive risk for surgery. Patients who are ≥ 65 years and diagnosed with severe pure AR as defined by the Echocardiographic Core Laboratory will be consecutively enrolled for further multidetector computed tomography (MDCT) scanning and multiplanar analyses. Based on a new anatomical classification and dual anchoring theory, patients will be classified into 4 types according to the level of the anchoring area. Types 1, 2 and 3 (at least 2 anchoring areas) will undergo the TAVR procedure with a domestic Chinese self-expanding valve (VitaFlow Valve, MicroPort, Shanghai, China), whereas type 4 (0 or 1 anchoring area) patients will be considered unsuitable for TAVR and will receive medical treatment. Our goal is to recruit 100 patients to account for 10% missing data or loss of patients to follow-up. Procedural, 30-day, 6-month and 12-month outcomes will be assessed according to Valve Academic Research Consortium-3 criteria.

**Discussion:**

The AURORA study will establish a new AR anatomical classification based on dual anchoring theory through MDCT multiplanar measurement and assess the safety and efficacy of TAVR guided by this new classification and strategy in AR patients.

*Trial registration*: This Study was registered at Chinses Clinical Trial Registry. The registration number: ChiCTR2200055415; The date of registration: 9, January 2022; The URL of the registration: http://www.chictr.org.cn/showproj.aspx?proj=141209.

## Background

Transcatheter aortic valve replacement (TAVR) has become the preferred treatment option in patients with severe aortic stenosis (AS) [1–3]. However, experience with applying TAVR in patients with pure native aortic regurgitation (AR) is limited. A recent epidemiological survey showed a prevalence of moderate to severe pure AR as high as 1.2% in China, and it was found to be the most frequent type of valvular dysfunction [4]. Even though patients with severe AR and left ventricular ejection fraction < 30% have an annual mortality risk of 20%, only 5% of the patients have an operation because of the high risk [5]. It thus becomes imperative to determine whether TAVR could be a feasible option in poor surgical candidates. However, AR is usually associated with abnormalities of the aortic cusp or root, without valvular calcification. These distinctive anatomical characteristics are extremely challenging to deal with when anchoring the device in TAVR (Fig. 1). Several registries have recently reported unsatisfactory outcomes of TAVR in patients with pure AR. The 30-day mortality rate has ranged from 9.3 to 23%. A total of 7.5–27.3% of patients required a new pacemaker; 0–4.7% had a stroke; 20.9–23% had moderate to severe paravalvular regurgitation; and 0–24.4% of patients needed a second transcatheter heart valve (THV) [6–10].

**Fig. 1 Fig1:**
[figure not shown]
Unique aortic root morphological characteristics of pure aortic regurgitation compared to calcified aortic stenosis. Lack of a calcified landing level is a main challenge for TAVR in pure aortic regurgitation patients (**A**); Calcified spots of native aortic stenosis provide anchoring level for transcatheter heart valve in TAVR procedure (**B**). TAVR = transcatheter aortic valve replacement

The presence of a double or multiple anchoring zones in the multiplane tract (from LVOT to ascending aorta) will significantly improves the stability of the prosthesis. A “TAVR-directed AR morphology classification” was proposed by our group. Based on this new classification and relevant procedure strategies, 32 cases of AR-TAVR using first-generation devices from China (The Venus A-Valve, Venus MedTech, China; VitaFlowTM transcatheter aortic valve, MicroPort®, Shanghai, China) have been performed before March 2021. The procedural success rate was 100% and the permanent pacemaker implantation rate was relatively low. These preliminary results are much better than many results using early-generation device reported by other centers. Therefore, we propose a prospective, multicenter, cohort study to evaluate the safety and efficacy of a novel **A**natomical classification and d**U**al ancho**R**ing theory to **O**ptimize the tav**R** strategy for pure severe **A**ortic regurgitation (AURORA).

The objectives of the proposed study are as follows:To construct an accurate morphological classification of aortic root anatomy in patients with severe pure AR to guide TAVR.To establish a novel double-anchoring strategy for transfemoral TAVR based on this new morphological classification.To evaluate the safety and effectiveness of transfemoral TAVR for patients with severe pure AR performed according to the double-anchoring theory and the new aortic root morphological classification.

## Methods

The AURORA study is a prospective, multicenter, single-arm, cohort study that will be conducted in 14 high-volume centers with specified expertise in TAVR. Patients with symptomatic pure severe AR confirmed by an Echocardiographic Core Laboratory who are ≥ 65 years will be consecutively enrolled for multidetector computed tomography (MDCT) scanning. After discussions with the heart team, the patients who are considered to have a prohibitive or high risk for surgery will be classified into 4 types: types 1, 2 and 3 patients who have more than 2 anchoring areas for THV will be treated with the TAVR procedure, whereas patients classified as type 4 who have only 1 area [either at the left ventricular outflow tract (LVOT), annulus, or ascending aorta (AA)] or no suitable area for anchoring will continue to receive medical treatment. Procedural and 30-day, 3-month, 6-month and 12-month outcomes will be assessed according to the Valve Academic Research Consortium-3 consensus (VARC-3 criteria). Enrollment is expected to be completed within 18 months. Institutional ethical approval will be requested in each center according to local regulations that comply with the principles outlined in the Declaration of Helsinki for research in human subjects. The study flow chart is depicted in Fig. 2.

**Fig. 2 Fig2:**
[figure not shown]
Study Flow Chart. *AR* aortic regurgitation, *ECL* echo core lab, *MDCT* multi-detector computed tomography, *TAVR* transcatheter aortic valve replacement

### Study population

#### Inclusion criteria

Pure severe AR diagnosed by echocardiography; ≥ 65 years old; high surgical risk or surgical contraindications as discussed by the heart team; MDCT multiplanar with measurements; and a signed informed consent form.

#### Exclusion criteria

Patients with AS diagnosed by echocardiography; left ventricular ejection fraction < 20% and left ventricular end-diastolic diameter > 70 mm; poor medical compliance; participation in other interventional clinical trials within the past 30 days. The details of the inclusive and exclusive criteria are listed in Table 1.

**Table 1 Tab1:** Study population

*Inclusion criteria*
1. Patients with pure severe AR diagnosed by echocardiography
2. > 65 years old
3. Patients with high surgical risk and surgical contraindications discussed by heart team
4. Multi-director computed tomography (MDCT) multiplanar measurements are complete
5. Informed consent form
*Exclusion criteria*
1. Patients with AS diagnosed by echocardiography
2. LVEF < 20% and LVEDD > 70 mm
3. Other contraindications for TAVR: Subjects with bacteremia or toxemia; active endocarditis; any intracardiac mass, left ventricular or atrial thrombus, vegetation diagnosed by echocardiography; severe mitral or tricuspid valve regurgitation; severe allergy to contrast agent, aspirin, heparin, thiazide, nickel-titanium memory alloy; other serious diseases that may reduce the life expectancy to less than 12 months; severe coagulation dysfunction; abdominal or thoracic aortic aneurysm; other conditions that the investigators determine are not suitable for this clinical study
4. Poor patient compliance, unable to complete the study as required
5. Have participated in other interventional clinical trials (within the past 30 days)

#### Protocol

The candidates will be screened and selected by our extended heart team, which includes an interventional cardiologist, a heart failure specialist, a cardiac imaging specialist, and a cardiac surgeon. The screening process includes an initial selection based on routine available measurements, dedicated confirmatory assessments (including echocardiography and MDCT), and final review by a central screening committee.

### Initial screening and informed consent

All patients with symptoms of heart failure and severe pure AR will be screened for eligibility to participate in the study by the local heart teams. The initial evaluation by the extended heart team is intended to evaluate the surgical risk based on routinely available information and to provide written informed consent to undergo the dedicated screening investigation and the subsequent morphological classification.

### Echocardiographic data analysis

The comprehensive transthoracic echocardiography or transesophageal echocardiography (if transthoracic echocardiography is suboptimal) data are uploaded to the Echocardiographic Core Laboratory for confirmation of the echocardiographic eligibility criteria. According to the 2017 American Society of Echocardiography guidelines [11], pure severe native AR is defined as severe AR without AS. The diagnosis of severe AR was based on the following criteria: (1) vena contracta width > 6 mm; (2) pressure half-time < 200 ms; (3) effective regurgitant orifice area ≥ 30 mm^2^; (4) regurgitant volume ≥ 60 ml/beats; and (5) dilation of the left ventricle.

### Multidetector computed tomography acquisition and analyses

#### Multiplanar analyses for anatomical characteristic of aortic root

Sixty-four-slice CT scans will be performed, using 100–120 kV, and tube current is modified according to patient size. All MDCT scans will be electrocardiogram-gated, primarily incorporating retrospective gating to yield a systolic phase for annular measurements. MDCT DICOM data are analyzed prospectively for all patients. Curved multiplanar reconstruction analyses will be performed using software specifically customized for valve analysis (3mensio Valves TM, version 10.1; 3mensio Medical Imaging BV, Bilthoven, The Netherlands).

A line is generated through the center point of the AA, aortic valve, annulus, and LVOT. The basal annular plane is defined as defined by the three basal attachment points of the aortic valve leaflets: the left-coronary cusp (LCC), the noncoronary cusp (NCC), and the right coronary cusp (RCC). A tracing of this annular plane provided maximal and minimal annulus diameters, area, and perimeter. LVOT, annulus, sinotubular junction (STJ), AA dimension 40 mm above the annulus, and maximal AA dimensions were measured routinely. Moreover, supra-annular and AA multiplanar dimensions (2, 4, 6, 8, 10, 30, 35, 40, 45, and 50 mm above the basal annular plane) will be also measured to identify the proper anchor levels for THV (Fig. 3).

**Fig. 3 Fig3:**
[figure not shown]
TAVR-specific AR dual-anchoring multiplanar measurements strategies. *TAVR* transcatheter aortic valve replacement, *AR* aortic regurgitation, *MDCT* multi-detector computed tomography, *AA* ascending aorta

### Multidetector computed tomography for vascular access suitability, including the aorta and iliofemoral axis

An aorta-ilio-femoral angiogram can be performed at the time of the preprocedural cardiac catheterization to facilitate vascular access evaluation, but this will not be a substitute for the MDCT.

### Transcatheter aortic valve replacement-directed aortic valve imaging: morphological classification

In a preliminary study, we found that the THV may be anchored at 3 areas in patients with pure AR: LVOT from − 4 to 0 mm below the aortic annulus, the annulus from 0 to 8 mm above the annulus, and the AA from the STJ to 40 mm above the annulus. THV anchoring was considered adequate if a perimeter oversizing index of > 10% was measured on the LVOT or the AA. A perimeter oversizing index of > 20% on a single annulus plane or of > 10% on every annulus area plane (0, 2, 4, 6, and 8 mm above the basal annular plane) is considered an adequate anchor on the annulus. If the THV can be anchored at more than two of the areas mentioned above with a considerable oversizing index rate, they are considered to have adequate anchoring stability for the TAVR procedure, which is termed the dual-anchoring theory**.**

Based on multiplanar measurements of aortic root anatomy and dual-anchoring theory, patients with AR will be classified into 4 types: Type 1: THV anchoring at the levels of the LVOT, the annulus, and the AA; type 2: THV anchoring at the levels of the annulus and the AA; type 3: THV anchoring at the levels of the annulus and the LVOT; type 4: THV anchoring at 1 level (either at the level of the LVOT, the annulus or the AA) or no anchoring at all.

Patients with AR with types 1, 2 and 3 THV anchoring will be candidates for TAVR, whereas those with type 4 THV anchoring will be assigned to continue optimal guideline-directed medical treatment for heart failure (Fig. 4).

**Fig. 4 Fig4:**
[figure not shown]
Schematic Diagram of TAVR-Directed AR Morphology Classification. Type 1: the LVOT, the annulus and supra-annular extending to ascending aorta can be anchored. Type 2: the LVOT cannot be anchored, but the annulus and ascending aorta can be anchored. Type 3: the annulus and LVOT can be anchored, but the ascending aorta cannot be anchored. Type 4: the LVOT, the annulus and supra-annular extending to ascending aorta cannot be anchored. THV anchoring was considered adequate if a perimeter oversizing index of > 10% was measured on LVOT or ascending aorta. Perimeter oversizing index of > 20% on single annulus plane or of > 10% on every annulus area planes (0, 2, 4, 6, 8 mm above the basal annular plane) is considered as anchoring adequate on annulus. Perimeter oversizing index was defined as [(device nominal perimeter)/(original perimeter measured by computed tomography)−1] * 100. AR Patients with type 1–3 can be candidates for TAVR, while type 4 is not suitable for TAVR treatment. *TAVR* transcatheter aortic valve replacement, *AR* aortic regurgitation

### Transcatheter aortic valve replacement procedure Devices

In this study, a domestic Chinese self-expanding TAVR device, the VitaFlow Valve (MicroPort, Shanghai, China) [12] will be used in patients with AR (Fig. 4).

### Procedures

All procedures will be performed with the patients given local or general anesthesia with intubation in the hybrid catheterization laboratory, under fluoroscopic guidance, by the multidisciplinary heart team. The transfemoral procedures will be performed as described previously [13, 14].

The following technical aspects will be investigated: (1) Releasing strategies: Rapid pacing (heart rate 180 beats/min) is recommended to decrease the regurgitation volume and systolic blood pressure. For patients classified as having type 2 anatomy, rapid pacing with 1 fast deployment will be used to improve the stability of the THVs. For patients with types 1 and 3 anatomical configurations, rapid pacing is used until two-thirds of the TAVR frame is released. Once the position is carefully checked with angiography, the THV is completely deployed. (2) Transcatheter aortic valve replacement-in-transcatheter aortic valve replacement technique: In patients in whom there is significant paravalvular regurgitation after the first THV deployment, it is suggested that a second THV should be implanted to reduce paravalvular regurgitation, malposition, or embolization of the first valve diving into the left ventricle.

### Study end points

The study end points will be defined according to VARC-3 criteria [15]. The primary efficacy end point is the device success rate. The second efficacy end point is the composite of technical success and improvement in AR severity after the procedure. Furthermore, we will investigate several additional secondary end points, including the rate of rehospitalization for heart failure, change in functional capacity as indicated by whether the patient is rated as the New York Heart Association functional class I or II, the 6-min walk distances, and the plasma concentration of N-terminal fragment brain natriuretic peptides (NT-proBNP) at 12 months compared with baseline. We will also assess myocardial remodeling by determining changes in the echocardiographic parameters of left ventricular remodeling at 12 months, as well as the quality of life utilizing the Kansas City Cardiomyopathy Questionnaire (KCCQ) score.

The safety end points include the major adverse cardiovascular and cerebrovascular events, which are defined as the composite end points of death, stroke, myocardial infarction, renal failure, arrhythmia, and conduction block occurring after the puncture, and reoperation for device- or procedure-related adverse events. All-cause mortality (30 days, 6 and 12 months after the procedure), cardiovascular mortality (30 days, 6 and 12 months after the procedure), and the post-procedure rehospitalization rate due to heart failure (30 days, 6 and 12 months after the procedure). All primary and secondary end points and the relationship of the event to the device and to the operation will be determined by an independent clinical event committee based on the prespecified definitions after review of the original medical documentation. The details of the study end points are summarized in Table 2. Details of the assessment performed during hospitalization and at each follow-up visit are depicted in Table 3. Follow-up visits are planned at 1 month, 6 months, and 12 months for all patients after discharge, irrespective of whether devices are implanted. Collection of routinely available clinical data will be discontinued only if explicitly request by the subject.

**Table 2 Tab2:** Study endpoints

*Primary efficacy endpoint*
Device success rate (at 30 days) according to VARC-3 criteria Technical success (at exit from procedure room) Freedom from mortality Successful access, delivery of the device, and retrieval of the delivery system Correct positioning of a single prosthetic heart valve into the proper anatomical location Freedom from surgery or intervention related to the device* or to a major Vascular or access-related, or cardiac structural complication Freedom from mortality Freedom from surgery or intervention related to the device or to a major vascular or access-related or cardiac structural complication Intended performance of the valve‡ (mean gradient < 20 mmHg, peak velocity < 3 m/s, Doppler velocity index ≥ 0.25, and less than moderate aortic regurgitation)
*Secondary efficacy endpoints*
Technical success rate
The rate of patients with AR ≤ 2 + after surgery (7 days after procedure/before discharge, 30 days, 6 months and 12 months)
The rate of postoperative hospitalization for heart failure (7 days after procedure/before discharge, 30 days, 6 months and 12 months)
The rate of NYHA class I or II after procedure (7 days after procedure/before discharge, 30 days, 6 months and 12 months)
Improvement of 6MWD from baseline (baseline and 12 months after procedure)
BNP/NT-proBNP improvement from baseline (baseline and 12 months after procedure)
Changes of echocardiographic LVEDV from baseline (baseline and 12 months after procedure)
Improvement of quality of life as assessed by the Kansas City Cardiomyopathy Questionnaire (KCCQ) score (baseline and 12 months)
*Safety endpoints*
Incidence of MACCEs during the study
Defined as the composite endpoints of death, stroke, myocardial infarction, renal failure, arrhythmia, and conduction block occurring after the puncture approach, and reoperation for device- or surgery-related adverse events
All-cause mortality (30 days, 6 and 12 months after procedure)
All-cause deaths include cardiac deaths, non-cardiac deaths, and unexplained deaths
Cardiac mortality (30 days, 6 and 12 months after procedure)
Post-procedure rehospitalization rate due to heart failure (30 days, 6 and 12 months after procedure)

**Table 3 Tab3:** Study data collection

Data collection	Baseline	Follow-up period				
		D1	D7/at discharge	D30	D180	D365
	− 7d	0d	0d	± 7d	± 15d	± 30d
Inform consent	X					
Demography	X					
Past history	X					
Vital sign	X		X	X	X	X
Physical Examination	X		X	X	X	X
History of angina	X		X	X	X	X
NYHA Functional Class	X		X	X	X	X
STS score	X					
Modified Rankin Scale (MRS) score	X		X	X	X	X
KCCQ score	X					X
6-min walk distance	X					X
ECG (18 leads)	X		X	X	X	X
TTE	X	X	X	X	X	X
MDCT	X				X	
CBC	X		X			
NT-proBNP	X					X
Coagulation Test	X		X			
Hepatic and renal function	X		X			
TNI/TNT	X		X			
Medication	X	X	X	X	X	X
Other treatments		X	X	X	X	X
AE/SAE Events	X	X	X	X	X	X

*NYHA* New York Heart Association, *STS* The Society of Thoracic Surgeon, *KCCQ* Kansas City Cardiomyopathy Questionnaire, *ECG* electrocardiography, *TTE* transthoracic echocardiography, *MDCT* multi-director computed tomography, *CBC* complete blood counts *NT-proBNP* N-terminal fragment brain natriuretic peptides, *TNT/TNI* troponins T and I, *AE/SAE* adverse events/severe adverse events

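### The NYHA secondary endpoint is described as a change but defined in Table 2 as an absolute post-procedure rate, so it partly reflects the class mix at entry

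*Protocol article*

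**What the plan says.** The protocol article gives the NYHA endpoint twice. In the text under Study end points it is "change in functional capacity as indicated by whether the patient is rated as the New York Heart Association functional class I or II". That sentence goes on to 6-minute walk distance and NT-proBNP and closes with "at 12 months compared with baseline". In Table 2, under the secondary efficacy endpoints, it is "The rate of NYHA class I or II after procedure (7 days after procedure/before discharge, 30 days, 6 months and 12 months", with no mention of baseline.

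On entry, Methods refers to "Patients with symptomatic pure severe AR confirmed by an Echocardiographic Core Laboratory", and Initial screening and informed consent states "All patients with symptoms of heart failure and severe pure AR will be screened for eligibility". Neither names an NYHA class. The formal inclusion list begins "Pure severe AR diagnosed by echocardiography; ≥ 65 years old; high surgical risk or surgical contraindications as discussed by the heart team" and contains no NYHA or symptom criterion. Nor does Table 1, of which the article says "The details of the inclusive and exclusive criteria are listed in Table 1".

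Table 3 schedules NYHA class at baseline, day 7 or discharge, day 30, day 180 and day 365. Statistical analyses names the χ² and Fisher exact tests for comparing categorical variables.

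**The concern.** A rate of patients in class I or II after the procedure is a state, not a change. It measures functional gain only if few patients were in that state beforehand, and the entry criteria do not secure this. Class II is a symptomatic class, so a class II patient fits every statement of eligibility in the article.

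The study has one arm, so no concurrent group shares the same baseline mix. A reader told that the item is a change in functional capacity will tend to take the whole rate as the effect of the strategy, although part of it may have been present at enrolment. Comparison with other series would have the same difficulty wherever their baseline class mix differs.

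**Working it through.** The article states no expected NYHA rate, baseline class distribution or power for this endpoint, so there is no figure to reproduce. The check has two parts.

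**1. Scoring under the Table 2 definition**

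| Baseline to visit | True course | Counts toward the rate? |
|---|---|---|
| III or IV to I or II | better | yes |
| II to II | unchanged | yes |
| IV to III | better | no |
| II to III or IV | worse | no |

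The second and third rows are where state and change part company.

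Within Table 2, the 6-minute walk, BNP/NT-proBNP and LVEDV items are worded relative to baseline, and KCCQ is an improvement assessed at baseline and 12 months. The NYHA item lists post-procedure visits only.

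**2. How far the baseline mix can move the rate**

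Inputs, both assumed because the article gives neither:
- b = share of patients in class I/II at baseline, all taken to stay there; range 10% to 40%.
- r = share of baseline III/IV patients who reach I/II; 0% or 60%.

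Formulas:
- Endpoint rate = b + (1 − b) × r
- Share of those counted who were already in I/II at entry = b / rate
- Group-level rise from baseline = rate − b = (1 − b) × r

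| b | Rate, r = 0 | Rate, r = 60% | Already in I/II among those counted, r = 60% | Rise from baseline, r = 60% |
|---|---|---|---|---|
| 10% | 10% | 0.10 + 0.90 × 0.60 = 64% | 0.10/0.64 = 16% | 54 points |
| 20% | 20% | 0.20 + 0.80 × 0.60 = 68% | 0.20/0.68 = 29% | 48 points |
| 30% | 30% | 0.30 + 0.70 × 0.60 = 72% | 0.30/0.72 = 42% | 42 points |
| 40% | 40% | 0.40 + 0.60 × 0.60 = 76% | 0.40/0.76 = 53% | 36 points |

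With no functional effect the rate equals b. With the same effect in III/IV patients throughout, it moves by 12 points (64% to 76%) on the entry mix alone. The last column shows that subtracting the baseline rate removes the floor but not the dependence on b. Only the rate among baseline III/IV patients returns r = 60% in every row.

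If one in ten baseline I/II patients worsens to III/IV, the rate is 0.9b + (1 − b) × 0.60: 0.09 + 0.54 = 63% at b = 10%, and 0.36 + 0.36 = 72% at b = 40%. The spread narrows to 9 points but remains.

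**The case against.** The strongest reply is that the sentence under Study end points closes with a comparison to baseline at 12 months. This can be read as covering the whole list, NYHA included, and the word for change at the start favours that reading. Table 3 collects NYHA class at baseline and at four later visits. On this reading the I/II proportion at 12 months is set against the I/II proportion at baseline, and the floor b becomes visible. A reader might infer from Table 2 alone that baseline class is never used; the documents do not support so firm a statement. What stands is that the reach of the phrase is unclear, that it names only 12 months while Table 2 lists four visits, and that Table 2 does not repeat it. The categorical tests named also treat the two sets as independent, although the same patients would appear in both.

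A reader might also infer that patients who get worse are routinely counted favourably. That needs a class I entrant who moves to class II. Table 1, whose first item is only "1. Patients with pure severe AR diagnosed by echocardiography", does not exclude such a patient, but the symptom wording in Methods and in the screening section makes one unlikely. A class II patient who worsens to III or IV is correctly not counted.

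It is also fair to say that Table 2 calls the item a rate, not a response, and that a post-procedure state is a legitimate descriptive outcome. Functional benefit is assessed by other measures too. The full protocol or analysis plan may specify a paired analysis; its absence from a condensed article is not the point here. The point is that the article's two statements of one endpoint disagree.

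**Conclusion.** The point holds as a mismatch between description and definition in one secondary endpoint. Unchanged class II patients count toward the rate and IV-to-III improvements do not, so the rate partly reflects the class mix at entry.

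The illustrated size is 64% to 76% for the same assumed 60% attainment among III/IV patients, as the assumed baseline I/II share goes from 10% to 40%. This is an identity worked on assumed inputs with no worsening among baseline I/II patients. It shows what the definition permits and does not estimate the bias in this trial. If nearly all entrants are in class III/IV, the effect is small.

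The primary endpoint, device success, and the sample size built on it are untouched.

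**What to change.** - Keep the rate of class I or II at each visit as a descriptive item, always shown beside the rate at baseline.
- Align Table 2 with the text under Study end points by defining the change endpoint within patient, against baseline class, at day 7 or discharge, 30 days, 6 months and 12 months.
- Present a baseline-to-visit shift table, and use a paired test (for example McNemar for I/II versus III/IV) in place of the unpaired χ² or Fisher test. McNemar on that split does not see a move from IV to III; the shift table does.
- Report attainment of class I/II among patients in class III/IV at baseline.

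Replacing the I/II rate outright with improvement by at least one class is debatable, since a class I patient cannot improve.

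The cost is endpoint and analysis wording only, because Table 3 already schedules every assessment needed. The III/IV subset has a smaller denominator, so its estimate will be less precise, and the reported rate may look less favourable.

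### Walk distance, KCCQ and NT-proBNP are measured after the procedure only at day 365, so their 12-month change describes surviving attenders only

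*Protocol article*

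**What the plan says.** In the protocol article, Table 2 (Study end points) gives three secondary efficacy endpoints as a change between two time points: "Improvement of 6MWD from baseline (baseline and 12 months after procedure"), "BNP/NT-proBNP improvement from baseline (baseline and 12 months after procedure") and "Improvement of quality of life as assessed by the Kansas City Cardiomyopathy Questionnaire (KCCQ) score (baseline and 12 months"). Table 3 (Study data collection) matches this. The rows for "6-min walk distance", KCCQ score and NT-proBNP are marked at baseline and D365 and nowhere between.

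Other measures are collected more often. Table 2 has "The rate of NYHA class I or II after procedure (7 days after procedure/before discharge, 30 days, 6 months and 12 months"), and Table 3 marks transthoracic echocardiography at every visit. The visits themselves take place: "Follow-up visits are planned at 1 month, 6 months, and 12 months for all patients after discharge, irrespective of whether devices are implanted". Deaths are a separate safety endpoint, "All-cause mortality (30 days, 6 and 12 months after procedure").

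The Statistical analyses section names unpaired tests (Student t or Mann–Whitney) for continuous variables and no paired test. It allows 10% for missing data or loss to follow-up when moving from 86 to 100 patients. The Background says of earlier registries: "The 30-day mortality rate has ranged from 9.3 to 23"%.

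**The concern.** Death before D365 is foreseeable in this population, and for three of the patient-level measures of benefit it removes the patient altogether. No earlier post-procedure reading exists to fall back on. This follows from the schedule of collection, so an analysis plan can choose how to treat deaths but cannot recover a questionnaire that was never given.

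The study has no control arm that would lose patients in the same way. A mean improvement from baseline to 12 months will naturally be read as what the classification-guided strategy achieves for the patients it treats. What it estimates is the change in those who lived and came back. If the patients lost would have done worse than those who remain, the figure flatters the strategy.

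The named tests could add a second distortion. If the baseline and 12-month means are compared as unpaired samples, patients who later die count in the first mean and not in the second.

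**Working it through.** **No planned figure to reproduce.** The article gives no sample size, power or expected change for these endpoints. Its 86 patients, raised to 100, concern device success at 30 days (86 / 0.90 = 95.6, so 100 covers the stated 10%). That allowance does not bear on this point.

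**Step 1. Who has a post-procedure value (Table 3).**

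| Measure | Post-procedure readings | Patient who dies between D180 and D365 |
|---|---|---|
| 6-minute walk | D365 | none |
| KCCQ | D365 | none |
| NT-proBNP | D365 | none |
| NYHA class | D7/discharge, D30, D180, D365 | up to three readings |
| Echocardiography (source of LVEDV) | D1, D7/discharge, D30, D180, D365 | up to four readings |

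The statement that no post-procedure value exists is therefore exact for the first three rows only.

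**Step 2. Possible size of the selection effect on a mean change.** Let f be the share dead or missing by D365, c the standard normal quantile of f, and r the correlation between the change and the tendency to survive and attend. With selection on a normal liability, the mean in attenders exceeds the mean in all treated patients by

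r × φ(c) / (1 − f) standard deviations of the change.

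Both inputs are assumptions. For f, I use the 9.3% to 23% cited in the Background as a stand-in for loss by 12 months. It is 30-day mortality in other registries. For r, I take 0.2 to 0.5.

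- f = 0.093: c = −1.32, φ(c) = 0.166, φ(c) / 0.907 = 0.183. With r = 0.2 to 0.5 the bias is 0.04 to 0.09 SD.
- f = 0.23: c = −0.74, φ(c) = 0.304, φ(c) / 0.77 = 0.394. With r = 0.2 to 0.5 the bias is 0.08 to 0.20 SD.

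Of 100 treated patients, about 91 (f = 9.3%) or 77 (f = 23%) would have a D365 value.

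**Step 3. The same results as a rate over all treated.** Suppose 70% of attenders improve (an assumption). Counting death and missing as not improved, the rate over all treated is 0.70 × 0.907 = 63.5% at f = 9.3% and 0.70 × 0.77 = 53.9% at f = 23%. This is a different quantity from the rate in attenders, and it answers the question that a reader of a single-arm study is likely to ask.

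**Step 4. The effect of an unpaired comparison.** Let S be the baseline mean in those who will attend at D365 and L the baseline mean in those who will not. The baseline mean in all patients is (1 − f)S + fL. If no patient changes at all, the 12-month mean is S. The apparent gain is S − [(1 − f)S + fL] = f(S − L). With an assumed KCCQ gap of 15 points, this is 0.10 × 15 = 1.5 points at 10% loss and 0.20 × 15 = 3 points at 20%. A paired within-patient change removes this component. It does not remove the selection in Step 2.

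**The case against.** The strongest reply is that the article is a condensed account. How deaths, missing visits and denominators enter the secondary endpoints is commonly left to the full protocol or analysis plan, so silence on this is no fault. That stands. It is why the point rests on the collection schedule, which the article does state.

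Several further objections also stand:

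- **Direction is not proven.** For a within-patient change, frailer patients may have the most room to improve. With a negative r in Step 2 the bias would reverse. An unfavourable course in those lost is plausible, but the document does not show it.
- **Mortality figures are borrowed.** The 9.3% to 23% comes from other registries at 30 days, and the 20% annual figure in the Background applies to LVEF below 30%. This study selects on anchoring anatomy and excludes patients expected to live less than 12 months.
- **Deaths are not hidden.** All-cause and cardiac mortality are reported at 30 days, 6 and 12 months. This lets a reader see the deaths, but it does not change what a mean in attenders estimates.
- **Earlier questionnaires help only in part.** A patient who dies before D30 would have no D30 KCCQ either. For these patients only an endpoint that gives death an outcome helps.

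A reader might infer that the NYHA, residual AR and heart-failure rehospitalization rates are also survivors-only. The article gives no denominator for them, and a rate over all treated patients fits its wording equally well. NYHA class and echocardiography also have earlier readings. A reader might go on to compute, from an assumed 85% in NYHA I or II among survivors, rates of 76.5%, 68% and 59.5% over all treated at 10%, 20% and 30% mortality, and call the difference of 8.5 to 25.5 points an overstatement. That is the gap between two different quantities. It becomes an error only under a survivors-only denominator that the article does not state.

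**Conclusion.** The point holds for walk distance, KCCQ and NT-proBNP. Their only post-procedure reading is at D365, so the mean 12-month change will describe surviving attenders, in a single-arm study of patients at high or prohibitive surgical risk. It may be too favourable as a statement of benefit.

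The size cannot be fixed from the document, which gives no 12-month mortality for this population. The range of about 0.04 to 0.20 SD is an illustration that depends on borrowed mortality and an assumed positive correlation. The unpaired tests would add to the problem only if they are the ones used for baseline versus 12 months, which the article does not say.

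The primary endpoint, device success at 30 days, includes freedom from mortality and is unaffected. The consequence is confined to what the 12-month functional results can support. The schedule part can be repaired only for patients whose D30 and D180 visits are still to come.

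**What to change.** **Table 3.** Add KCCQ at the existing D30 and D180 visits.

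**Table 2.** For KCCQ and walk distance, add a supplementary rate of patients alive and improved from baseline at 12 months. The denominator is all patients in whom TAVR was attempted, the improvement threshold is prespecified, and death counts as not achieved. State the 12-month NYHA endpoint over the same denominator, as alive and in class I or II. This settles a denominator that is now open.

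**Reporting.** Label the mean changes as survivors-only, compute them as paired within-patient changes, and print the numbers dead and missing beside each. In the Statistical analyses section, name a paired method for baseline versus 12 months.

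**Cost.** One questionnaire at two visits that already take place, some wording in Table 2 and the statistical section, and 12-month figures that will look less favourable. Walk distance and NT-proBNP would remain D365-only. For walk distance, the alive-and-improved rate covers the gap. For NT-proBNP, the survivors-only label and the counts must do so.
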